## Abstract

**Background:**

Body weight loss (BWL) after gastrectomy impact on the short- and long-term outcomes. Oral nutritional supplement (ONS) has potential to prevent BWL in patients after gastrectomy. However, there is no consistent evidence supporting the beneficial effects of ONS on BWL, muscle strength and health-related quality of life (HRQoL). This study aimed to evaluate the effects of ONS formulated primarily with carbohydrate and protein on BWL, muscle strength, and HRQoL.

**Methods:**

This will be a multicenter, open-label, parallel, randomized controlled trial in patients with gastric cancer who will undergo gastrectomy. A total of 120 patients who will undergo gastrectomy will be randomly assigned to the ONS group or usual care (control) group in a 1:1 ratio. The stratification factors will be the clinical stage (I or ≥ II) and surgical procedures (total gastrectomy or other procedure). In the ONS group, the patients will receive 400 kcal (400 ml)/day of ONS from postoperative day 5 to 7, and the intervention will continue postoperatively for 8 weeks. The control group patients will be given a regular diet. The primary outcome will be the percentage of BWL (%BWL) from baseline to 8 weeks postoperatively. The secondary outcomes will be muscle strength (handgrip strength), HRQoL (EORTC QLQ-C30, QLQ-OG25, EQ-5D-5L), nutritional status (hemoglobin, lymphocyte count, albumin), and dietary intake. All analyses will be performed on an intention-to-treat basis.

**Discussion:**

This study will provide evidence showing whether or not ONS with simple nutritional ingredients can improve patient adherence and HRQoL by reducing BWL after gastrectomy. If supported by the study results, nutritional support with simple nutrients will be recommended to patients after gastrectomy for gastric cancer.

**Trial registration:**

jRCTs051230012; Japan Registry of Clinical Trails. Registered on Apr. 13, 2023.

**Supplementary Information:**

The online version contains supplementary material available at 10.1186/s13063-024-08169-8.

## Background and rationale {6a}{6a-p}{7}{7-p}

Gastric cancer is the fifth most-common cause of cancer and third most-common cause of death worldwide [1]. Gastrectomy remains the main component of gastric cancer treatment. However, gastrectomy impairs the capacity of food retention and oral intake, which cause body weight loss (BWL) and decreased muscle mass [2, 3], muscle strength [4, 5] and health-related quality of life (HRQoL) [6]. Moreover, BWL after gastrectomy decreases patient adherence with adjuvant chemotherapy and worsens long-term prognosis [7–11]. Therefore, it is important to control the BWL after gastrectomy of patients with gastric cancer.

As recommended by the European Society of Clinical Nutrition and Metabolism (ESPEN) guidelines [12], oral nutritional supplements (ONS) have become an important part of postoperative nutritional management of patients with cancer. However, the outcomes of ONS after gastrectomy for patients with gastric cancer have been inconsistent [13–17]. A subgroup analysis of a systematic review also suggested no significant differences in weight loss between the ONS group and control group [18], although there was heterogeneity among studies in the type, amount, and content of ONS and duration of intervention.

It is believed that good ONS adherence is necessary to reduce BWL through intervention with ONS [16]. One of the barriers to maintaining patient adherence is the dislike of the flavor, texture, and viscosity of ONS [19]. It is commonly known that ONS formulations can lose their texture as a result of their complex nutrient content, and it is difficult to achieve a balance between comprehensive nutrition and the elements of ONS that promote patient adherence. In fact, it remains unclear if these comprehensive nutrients are actually essential for patients after gastrectomy who are not completely unable to take oral nutrition, although a previous study used a comprehensive supplement (i.e., trace elements, vitamins, n-3 fatty acid or fats) [13–17]. The main hypothesis for this study is that simple and smooth products that mainly include carbohydrates and proteins will reduce BWL of patients after gastrectomy compared to a regular diet.

Another important nutritional marker is muscle strength. In a clinical setting, handgrip strength that can be easily measured, recognized as one of criteria for examining the occurrence of sarcopenia [20]. Moreover, some studies have shown the effects of nutritional support for cancer patients on handgrip strength [21–23]. However, in a recent systematic review of ONS for gastric cancer patients, none of the included studies reported this outcome. We will include this important outcome in this study.

We also hypothesized that a simple ONS has the potential to improve the HRQoL after gastrectomy. ONS was previously found to improve some domains of HRQoL, including emotional function, global QOL, dyspnea, and appetite loss, in malnourished patients with cancer in a meta-analysis [24]. Moreover, previous studies have reported that various types of nutritional support improve overall HRQoL, physical function, role function, fatigue, and appetite loss [25–28]. However, few previous studies have assessed the effect of ONS on HRQoL in patients with gastrectomy. Although a few studies have reported that there was no significant difference between the ONS group and control group, it is unclear if any ONS can improve any of the domains of HRQoL in patients who have undergone gastrectomy for gastric cancer [14, 17].

The aim of the study described by the presented protocol is to evaluate the effect of ONS with carbohydrate and protein on BWL, muscle strength, and HRQoL.

### Trial design {8}

This study was designed as an open-label, multicenter, parallel-group, randomized controlled trial (RCT). Patients will be randomly allocated 1:1 into two groups to compare the efficacy of ONS with that of usual care. The study protocol follows the Standard Protocol Items: Recommendations for Interventional Trials Patient-Reported Outcome extension (SPIRIT-PRO [29]) checklist (Additional file 1) and the Template for Intervention Description and Replication (TIDieR) checklist and guide [30]. The description of interventions recommended by TIDieR can be found in Additional file 2. The flow diagram for recruitment and randomization is shown in Fig. 1.

**Fig. 1 Fig1:**
[figure not shown]
Flow diagram of the study design

## Methods: Participants, interventions and outcomes

### Study setting {9}

This RCT is organized by the Kyoto Esophageal and Gastric Cancer Surgery Group (KEGG), and the participants will be recruited at the Kyoto University Hospital and 18 affiliated hospitals.

#### Eligibility criteria{10}{13}

To avoid bias due to oncological factors or severe complications affecting endpoints and to ensure patient safety, this RCT plans to use a two-stage recruitment strategy. The inclusion and exclusion criteria are shown in Table 1.

**Table 1 Tab1:** Inclusion and exclusion criteria

**Inclusion criteria**
1) Aged 18 - 85 years
2) ECOG Performance Status (PS) 0-2
3) Oral intake will be possible postoperatively
4) Pathologically diagnosed epithelial malignancy of stomach (adenocarcinoma, squamous cell carcinoma, adenosquamous carcinoma, etc.)
5) cStage I-IVA or CY1P0
6) Scheduled for radical gastrectomy (distal gastrectomy, pylorus preserving distal gastrectomy, proximal gastrectomy, total gastrectomy)
7) Esophageal invasion length is within 2 cm or no esophageal invasion
8) Written informed consent was obtained
**First exclusion criteria (Preoperative exclusion criteria)**
1) Combined resection of liver, pancreas, colon (D1 resection or over) or/and paraaortic lymph node
2) Remnant gastric cancer
3) Diagnosis of double cancer
4) Allergic to Isocalclear (e.g. milk allergy)
5) Have advanced renal dysfunction (eGFR < 30mL/min/1.73m2)
6) Treated with insulin or poorly controlled diabetes mellitus.
7) Have organ dysfunction requiring strict restriction of drinking water.
8) Have psychiatric disorders or psychiatric symptoms that interfere with daily life
9) Participants judged otherwise unsuitable for participation by the investigators.
**Secondary exclusion criteria (postoperative; POD5-7)**
1) cM1(distant metastasis) or R2 resection (except for CY1)
2) Combined resection of liver, pancreas, colon (D1 resection or over) or/and paraaortic lymph node, esophagectomy
3) Unable to begin an oral diet due to a complication( e.g. anastomotic leakage and so on)
4) Gastrectomy was not performed
5) Allergic to Isocal^®^clear (e.g. milk allergy)
6) Refuse to participate in this study

#### Who will take informed consent? {26a}

A study investigator at each institution will identify potential participants during outpatient clinic visits.

#### Additional consent provisions for collection and use of participant data and biological specimens {26b}

Not applicable.

## Interventions

### Explanation for the choice of comparators {6b}

The choice of comparators is usual care in this study, because there is no optimal nutritional choice to prevent BWL after gastrectomy. So, the selection as comparators is justified. Patients assigned to the control group will receive a regular diet without ONS, with any nutritional supplements allowed as needed.

#### Intervention description {11a}{13}{13-p}{20c}

Patients assigned to the ONS group will receive two 200 ml (400 kcal) volumes of ready-to-drink and recloseable packaging products (ISOCAL® clear) per day added to their regular diet. Each 200-ml pack of ISOCAL® clear contains 200 kcal, 40 g of carbohydrate, 10 g of whey protein, no fat, 166 g of water, and 0 g of sodium. Patients will start the intervention as soon as possible after secondary enrollment, which is the timing of randomization and allocations and will be 5 to 7 days after gastrectomy. The intervention continues until 8 weeks after surgery, so the duration could vary between patients. Investigators will advise patients on how to consume the products in 1 day by presenting a short movie or study brochure.

### Criteria for discontinuing or modifying allocated interventions {11b}{18b(ii)-p}

The assessments, including HRQoL questionnaires, will be continued unless the participants withdraw consent for assessments. The following criteria will be used to discontinue the intervention:The participant requests discontinuation of the explanatory treatment.The participant cannot continue the explanatory treatment due to adverse events.The patient is found to be ineligible after initiation of treatment.The patient stops coming to the hospital due to relocation, etc.The patient dies.The study investigator determines that it is not appropriate to continue the explanatory treatment for any other reasons.

Unless the participant wishes to have his/her data destroyed or excluded, his/her already collected data will be retained and analyzed.

### Strategies to improve adherence to interventions {11c}

During the intervention period, the patients will be required to keep a daily diary (ONS diary) that includes the amount of daily ONS consumed. Each investigator will monitor and resolve issues and questions about interventions during the hospital stay until discharge. Moreover, the investigators will check the ONS diaries at the outpatient clinic 1 month after surgery to improve adherence and minimize missing data in the ONS diary. The study schedule is shown in Fig. 2.

**Fig. 2 Fig2:**
[figure not shown]
Study schedule

### Relevant concomitant care permitted or prohibited during the trial {11d}

There are no restrictions regarding concomitant care during the trial. If the primary physician determines that nutritional intervention is necessary for the treatment of nutritional disorders, any nutritional supplement will be allowed. However, the patients who preoperatively plan to take any nutritional supplements after surgery will be excluded at the enrollment.

Patients in both study groups will be allowed to take any medicine including prokinetic agents or antidiarrheal agents, and any additional ONS as necessary.

### Provisions for post‑trial care {30}

Patients who will suffer harm by participating in this trial will be covered by the Japanese public health care system and the insurance for this study.

## Surgical procedure and postoperative management

The clinical and pathological stages of the malignancies were based on the Japanese Classification of Gastric Carcinoma [31]. Patients will undergo standard gastrectomy and lymph-node dissection according to the Japanese Gastric Cancer Treatment Guidelines, 6th edition [32]. Moreover, the standardization of the gastrectomy techniques has been established through the KEGG regular meetings. The surgeons choose the surgical approach (i.e., open or minimally invasive surgery) and reconstructive method according to their experience. For distal gastrectomy (DG), we will perform Billroth I (DG-BI), Billroth II (DG-BII), or Roux-en-Y reconstruction (DG-RY). For proximal gastrectomy (PG), we will perform esophagogastrostomy (PG-EG), double-tract method (PG-DT), or another reconstruction method. For total gastrectomy (TG), Roux-en-Y reconstruction (TG-RY) will be performed. When there is an esophageal invasion, transhiatal esophageal resection will be performed.

Patients will be allowed to drink water and ingest a solid diet according to the postoperative protocol of each institution. Patients will be discharged home when their primary-care physician approves. The intervention will be started before discharge in the ONS group. Patients with pathological stage II or III disease will receive adjuvant chemotherapy (AC) by S-1 with/without docetaxel or another regimen according to the Japanese Gastric Cancer Treatment Guidelines, 6th edition [32]. AC is usually started within 4–8 weeks [33, 34]. Because the duration until the primary outcome measurement time point is short and the study design is an RCT, the potential for bias due to AC is thought to be minimal.

### Outcomes {12}

Evaluations will be performed before surgery (T1) and at 8 weeks (T2), 6 months (T3), and 12 months after surgery (T4). Baseline measurements (T1) of laboratory data are to be collected within 45 days prior to surgery, and the other outcome measures including body weight, handgrip strength and HRQoL are to be collected within 14 days prior to surgery. In particular, body weight will be required to be measured at a time as close to the date of surgery as possible at T1 and will be measured at T2 to T4 using the same weight scale and with patients in light clothing as at T1.

## Primary outcome measure

The %BWL from T1 to T2 after surgery will be the primary outcome in this study. To minimize the measurement bias between each time point, the same weight meter at each institution will be used under similar conditions, such as clothes and time after meal.

### Secondary outcome measures {12-p}{18a(i)-(iii)-p}{18b(ii)-p}

The secondary endpoints are as follows:The %BWL from T1 to T3 and T4Change in handgrip strength from T1 to T2, T3, and T4HRQoL at T2, T3, and T4 {13-p}To assess HRQoL, the following validated and widely used instruments will be used: the European Organization for Research and Treatment of Cancer Quality of Life Questionnaire Core-30 (EORTC QLQ-C30) [35] and EORTC QLQ-OG25 [36]. The EQ-5D-5L[37] will be used to measure the Health Utility Index. The cancer-specific health-related QOL questionnaire (QLQ-C30) consists of 30 questions in 15 subscales: one scale for global QOL, five scales focusing on function (physical, social, role, cognitive, and emotional), and three symptom scales (fatigue, pain, vomiting/nausea), and six single-item scales (insomnia, appetite loss, dyspnea, constipation, diarrhea, and financial difficulties). The QLQ-OG25 is an esophago-gastric–specific module comprising 25 questions in six subscales (dysphagia, eating restrictions, reflux, odynophagia, pain, and anxiety). This study can include some patients with gastro-esophageal junction cancer, and the QLQ-OG25 is reportedly more sensitive than the EORTC QLQ-STO22 [38] for evaluating the QOL of patients after TG. The EQ-5D-5L consists of five dimensions (mobility, self-care, usual activities, pain/discomfort, and anxiety/depression) with five levels (no, slight, moderate, severe, and extreme problems/unable to). Quality-adjusted life years will be calculated according to the Health Utility Index estimated from the EQ- 5D. Japanese versions of these questionnaires have been developed [39–41].

4)Hematologic and blood chemistry (hemoglobin, lymphocyte count, albumin) at T2, T3, and T4.5)Dietary caloric intakes at T1 and T2.Dietary caloric intakes will be assessed by a dietitian at the 14 institutions where dietitians can collaborate with the study researchers. We will use the larger 66-item Food Frequency Questionnaire (short-FFQ), which was developed for the Japan Public Health Center-based prospective Study for the Next Generation (JPHC-NEXT) [42]. Food and nutrient intake will be calculated on designated computer software (FFQ NEXT, Kenpakusha, Tokyo, Japan) based on Standard Tables of Food Composition in Japan 2020 (8^th^ revised edition). At T2, the patients will be required to answer the questions according to their dietary intake after gastrectomy.

6)Adverse eventsAdverse events will be evaluated by the Common Terminology Criteria for Adverse Events (CTCAE) ver5.0 of the National Cancer Institute of the United States.

7)Adherence to ONS.In the ONS group, adherence to ONS will be measured through the patients’ daily ONS diary. The average amount of ONS consumed per day and the percentage of patients who can consume greater than 200 ml of ONS per day will be calculated.

#### Participant timeline {13} {13-p}

The patient timeline is shown in Fig. 3.

**Fig. 3 Fig3:**
[figure not shown]
Content for the schedule of enrollment and assessments

### Sample size {14}

The results of previous studies [10, 43–46] showed that the estimated mean percentage of the BWL at 8 weeks after surgery for gastric cancer is approximately 8%, with a standard deviation of approximately 5.5%. We anticipate that this percentage might be reduced to 5% in the ONS group, with a mean difference of 3%. To detect this difference, this RCT will require 106 participants for a two-sided significance level of 0.05 and 80% statistical power. The estimated total sample size is approximately 120 (60 patients per group) considering patients probably lost to follow-up and dropouts of approximately 10% from the 1st to 2nd enrollments.

#### Recruitment {15} {26a}

Patients will have the study explained by a study investigator and be enrolled preoperatively if they meet all of the inclusion criteria and none of the exclusion criteria (First enrollment). Each investigator will undergo secondary enrollment from 5 to 7 days after gastrectomy. An Electronic Data Capture (EDC) system made by this study data center (Zenbe Co., Ltd.; https://www.zenbe.jp/, accessed Jun 18, 2023) will be used to perform all enrollment and allocation. The data center is responsible for treatment allocation and data management.

## Assignment of interventions: allocation

### Sequence generation{16a}

Software developed by Zenbe Co., Ltd. and the stratified block method with permuted blocks will be used to perform the randomization under the supervision of the independent statistician (AN). The group sizes will be balanced according to clinical stage (I or ≥ II) and surgical procedure (TG or non-TG).

### Concealment mechanism{16b}

At the same time as the secondary enrollment via the EDC system, the random allocation will be performed and opened to the investigator. Allocation concealment will therefore be ensured.

### Implementation{16c}

After the allocation, the ONS group will start the protocol intervention as soon as possible.

## Assignment of interventions: Blinding

### Who will be blinded {17a}

In this open-label study, patients, physicians, and statisticians will be aware of the intervention assigned.

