### Data management {19}

Each patient will be coded with a research number via the EDC system at first enrollment, and their data will be collected via the EDC system. To improve the data quality, the EDC is designed to prevent the input of unrealistic values. Independent of statistical analysis by the statistician, all data will be checked before analysis by the data center.

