## Sensitivity analyses

We will perform sensitivity analyses using a full analysis set (FAS) and a per protocol set (PPS). The FAS analysis will exclude participants who never ingest the ONS in the ONS group and those who are later found not to meet the eligibility criteria from the population for the ITT analysis. The population for the PPS analysis will comprise participants who ingested an average of ≥ 200 ml of the ONS per day.

We will also perform sensitivity analyses using a generalized linear mixed model with repeated measures analysis to estimate the mean difference in the change of the percentage of BWL.

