### Methods in analysis to handle protocol non-adherence and any statistical methods to handle missing data {20c} {20c-p}

All analyses will be on an intention-to-treat (ITT) basis. Randomized patients will be included and will be analyzed according to their allocated group regardless of what postoperative management they received. We will exclude the patients who have no available data and with protocol violations, such as patients who are later found not to meet the eligibility criteria.

We will document the amount of and reasons for missing data, if possible, between the ONS and control group. In case of dropout, we will describe the timing of dropout and, if possible, the reason.

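### The statistician is unmasked by choice while exclusions from the primary population stay open-ended; a coded dataset and a closed exclusion rule would cheaply reduce the risk of arm-aware exclusions

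*Protocol article*

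**What the plan says.** All references are to the protocol article.

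- **Who will be blinded {17a}:** in this open-label study "patients, physicians, and statisticians will be aware of the intervention assigned". No reason is given for including the statisticians.
- **Methods to handle non-adherence and missing data {20c}:** all analyses are intention-to-treat (ITT), and randomised patients "will be analyzed according to their allocated group regardless of what postoperative management they received". The same paragraph then says: "We will exclude the patients who have no available data and with protocol violations". Late-found ineligibility is given as an example of a violation, not as the whole list.
- **Sensitivity analyses:** the FAS leaves out ONS-arm patients who took none of the supplement, and anyone in either arm who turns out to have been ineligible. The starting point for this set is the ITT population.
- **Recruitment {15}:** "The data center is responsible for treatment allocation and data management".
- **Data management {19}:** "Independent of statistical analysis by the statistician, all data will be checked before analysis by the data center".
- **Analysis of primary endpoint:** an independent t test on percentage body weight loss from baseline to 8 weeks.

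**The concern.** Fixing the test in advance does not fix the set of patients it is run on. Here that set depends on rulings made after randomisation, from a list with no stated end. The article names nobody to make the rulings and sets no time for them relative to the week-8 weights. A masked analyst would be one safeguard, but the plan states that the analyst is not masked.

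The primary comparison is at stake. Patients and physicians are unavoidably unmasked in this trial, so the analysis stage is one of the few places where masking remains possible. A few exclusions that depend on both arm and outcome would bias the treatment difference. The same number made without knowledge of arm would hardly move it.

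**Working it through.** **1. The text on who is in the primary population.** The non-adherence section removes ineligible patients from the ITT analysis. The sensitivity section removes them again, from the ITT population, to form the FAS. Both cannot describe the same ITT set: either the ineligible are in the primary analysis and the FAS drops them, or they are already gone and that part of the FAS rule is empty. Some eligibility rules also leave room for later argument. Table 1 includes poorly controlled diabetes and an investigator's judgement of unsuitability. The concomitant-care section adds a further exclusion (a preoperative plan to take supplements) that Table 1 does not list.

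**2. Who knows the arm.** Statisticians know it by the blinding section. Investigators know it because allocation is opened to them at secondary enrolment. The data centre knows it because it performs the allocation.

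**3. The plan's own sample size.** Inputs from the sample size section: difference 3, SD 5.5, two-sided alpha 0.05, power 80%.

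n per arm = 2 × (1.96 + 0.8416)² × 5.5² / 3² = 2 × 7.849 × 30.25 / 9 = 52.8, so 53 per arm and 106 in total, as stated. With 10% loss, 106 / 0.9 = 117.8, so 118, in line with about 120. Masking the analyst changes none of this.

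**4. Illustration with six reviewable patients.** Assumptions: 60 per arm, both arms Normal(8, 5.5), no true effect. Six randomly chosen ONS patients are open to a ruling, and the one or two with the greatest loss are dropped. The six, and the worst-first selection, are assumptions and not figures from the document. The two largest of six standard normal values have expectations 1.267 and 0.642.

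- One dropped: shift = 5.5 × 1.267 / 59 = 0.118 points. Standard error = 5.5 × √(1/59 + 1/60) = 1.008. Ratio 0.117. Chance of a false positive favouring ONS ≈ P(Z > 1.96 − 0.117) = 3.3%.
- Two dropped: shift = 5.5 × (1.267 + 0.642) / 58 = 0.181 points. Standard error = 5.5 × √(1/58 + 1/60) = 1.013. Ratio 0.179. Chance ≈ P(Z > 1.781) = 3.7%.

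Simulation with 20,000 to 40,000 replicates gave the same shifts and 3.4% to 3.9%, against 2.5% with no exclusions. The gap from the approximation is small.

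**5. Extreme case and the arm-blind contrast.** Here every patient is treated as removable. The ONS-only rows use 40,000 simulated trials and the pooled row 10,000, again with no true effect.

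| Worst outcomes removed | Spurious benefit (points) | Two-sided type I error |
|---|---|---|
| 1, ONS arm only | 0.22 | 6.0% |
| 2, ONS arm only | 0.40 | 7.8% |
| 3, ONS arm only | 0.58 | 10.0% |
| 4, ONS arm only | 0.74 | 12.9% |
| 1 to 4, from both arms pooled, arm unknown | about 0.01 | 5.3–5.5% |

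With no removal the same simulation gave about 5.2%, so the pooled row is close to nominal. The harm comes from knowing the arm and the outcome together.

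**The case against.** The strongest reply is that nothing in the document gives exclusion rulings to the statistician. Pre-analysis checking belongs to the data centre, separately from the statistician. The people most likely to discover late ineligibility are the investigators and data managers, who know the arm and would still know it under any recoding. Every figure above comes from the open exclusion rule; with all randomised patients kept, an unmasked analyst could not produce it. Eligibility is also screened twice, the second time at the point of randomisation on days 5 to 7, so late-found ineligibility should be uncommon. The 10% in the sample size section describes losses that include those between the two enrolments, so it does not support six reviewable patients in one arm. Finally, who adjudicates and when populations are locked is commonly left to an analysis plan, which is not shown.

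Much of this stands. It rules out three stronger readings that a reader might infer:

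- **That the statistician will choose whom to exclude.** The document does not say so.
- **That coding the arms would prevent arm-aware exclusions.** It would not, because others who know the arm can feed the list.
- **That analyst discretion over mixed models threatens the primary result.** The primary analysis is a t test. Mixed models serve the quality-of-life outcomes and a sensitivity analysis.

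Two things survive. The unmasked statistician is a stated choice that a separate analysis plan could not reverse without contradicting the article. The open list and its conflict with the FAS are also on the page.

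**Conclusion.** The concern holds as a cheap improvement, not as a demonstrated bias. The plan affirmatively leaves the statistician unmasked without need, while the primary population can be altered after randomisation by an open-ended and internally inconsistent rule. Together these make exclusions that depend on arm and outcome possible.

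Under the six-patient assumption the effect is modest: 0.12 to 0.18 points, or 4% to 6% of the planned 3-point difference (0.12/3 and 0.18/3), with one-directional error of about 3.3% to 3.9% instead of 2.5%. The larger figures in the table treat every ONS patient as removable and are an outer limit, not a forecast. All of these figures assume deliberate or unconscious selection of the worst outcomes in one arm, for which the document offers no evidence.

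**What to change.** 1. **Blinding section:** state that patients and physicians are unmasked but the analysing statistician is not. The data centre supplies an export with arms coded A and B, withholding ONS diary, intake and intervention-discontinuation fields, which would reveal the code.
2. **Non-adherence and missing data section:** preferably keep all randomised patients in the primary analysis, and report those without a week-8 weight by arm as missing data. Otherwise, close the list to eligibility facts that predate randomisation, judged by people who see neither arm nor outcome.
3. **Sensitivity section:** reconcile the FAS with the ITT definition, so that ineligible patients are removed in one place only.
4. **Order of work:** lock the population, run the week-8 t test on coded data, then open the code for the FAS, per-protocol and adherence analyses.

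Sample size and power are unchanged. The cost is a few sentences and a recoded export from a data centre that already holds the allocation and checks the data; that this is cheap is a judgement, as the document gives no costs. The small downside is that the FAS and per-protocol analyses wait for the code to be opened. Recruitment has closed, so only the analysis stage is affected. Steps 1 and 2 work together: coding alone leaves the open list in place, and investigators and the data centre will still know the arm.
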